15.5. Visit 4 (week 4)

|  | Symptom Assessment, Vital Parameters |
| --- | --- |
|  | Brief Ayurvedic Evaluation |
|  | Laboratory work up |
|  | Pulse Oximetry |
|  | Monitor Adverse Events |
|  | Health Related-Behaviour Fitness (HR-BHF) VAS questionnaire, Self-Reported Questionnaire (Mobile app) |
|  | Drug Compliance, Dispense study medication |

15.6 .Visit 5 (week 8)

|  | Symptom Assessment, Vital Parameters |
| --- | --- |
|  | Comprehensive Ayurvedic Evaluation |
|  | Medical History, Comprehensive Physical examination |
|  | Laboratory work up |
|  | Pulse Oximetry |
|  | Monitor Adverse Events |
|  | Health Related-Behaviour Fitness (HR-BHF) VAS questionnaire, Self-Reported Questionnaire (Mobile app) |
|  | Drug Compliance, Dispense study medication |
|  |  |

15.7. Visit 6 (Week 12)

|  | Symptom Assessment, Vital Parameters |
| --- | --- |
|  | Comprehensive Ayurvedic Evaluation |
|  | Medical History, Comprehensive Physical examination |
|  | Laboratory work up |
|  | Pulse Oximetry |
|  | Monitor Adverse Events |
|  | Health Related-Behaviour Fitness (HR-BHF) VAS questionnaire, Self-Reported Questionnaire (Mobile app) |
|  | Drug Compliance |
|  | Completion Report |

# 16. INVESTIGATIONAL DRUGS AND DOSING

The investigational drugs to be used individually in 3 separate drug trials of 2 arms each in this protocol are Sanshamani Vati Plus, AYUSH 64 and *Glycyrrhiza glabra*. The dosage schedule for each one of them is as follows:

i) AYUSH-64: 500 mg tablet, 2 tablets bid (twice daily)

ii) Yashtimadhu: 300 mg tablet, 2 tablets bid (twice daily)

iii) Sanshamani Vati Plus: Each tablet to contain 300 mg Guduchi plus 75 mg Pippali, 2 tablets bid (twice daily) with warm water.

**Botanical Test Material:** The ingredients of all the test materials used in this clinical study as investigational drug formulations are aqueous botanical extracts. All the botanical test materials (*Tinospora cordifoila, Piper longum, Alstonia scholaris, Picrorhiza kurroa, Swertia Chirata, Caesalpinia crista,* and *Glycyrrhiza glabra*) are manufactured in accordance with highest quality standard requirements. The test material formulation will be manufactured at GMP compliant facility using WHO guidelines on good herbal processing practices for herbal medicines (2017). The test material has been prepared from high quality botanical material carefully procured through approved vendor qualification program and authenticated by In-House taxonomist for each batch. The test material formulation has been tested as per the quality control requirements of Indian Pharmacopeia (2018) to analyze at least two analytical markers by HPLC for consistent fingerprinting and quality of finished products. LCMS profile may be obtained to ensure consistency in ratio of main peaks. The other mandatory testing includes heavy metals analysis, microbiological parameters, aflatoxins, residual solvents, and ash or water content to be carried out In-house for each batch of formulations (tablet) by the quality control department. Current certifications at the facility where test drugs will be prepared include Quality Management System (ISO 9001:2015), Food safety management (ISO22000:2005), NSF-GMP (21 CFR 111 & 117) with Kosher and Halal, and USDA/APEDA organic certifications for liable products. The facility premises contain a separate area for quality assurance, quality control, and research development departments. The manufacturer will produce valid Certificate of Analysis for every batch. The facility where test materials are prepared has well-structured and secured premises guarding the area with CCTV enhanced security systems. In short, the botanical test materials will be manufactured as one batch in accordance with Indian and WHO standards for AYUSH / herbal / botanical drugs. The reference samples of the raw material and extract will be preserved.

The medicines and other interventions being used as standard of care will be documented systematically with its dosage, duration, manufacturing company etc. The variations in the interventions being implemented as standard of care, if any, will be noted in case record form.

**16.1 Compliance:**

The number of tablets and capsules dispensed at each visit will be recorded in the medication log. On each return visit, the patient will be instructed to bring all unused medication and a “pill count” will be performed and recorded in the medication log.

**16.2 Concomitant Medication/Therapy:**

Patients will continue to consume any medication for concomitant illness like diabetes etc. permitted as per exclusion criteria and the under supervision of their primary care physician. Other medications required for any other illness during the study will be taken under supervision of the prescribing physician but the same will be informed to the study investigator.

Concomitant medications are to be kept to a minimum during the study. However, if these are considered necessary for the patient’s welfare and do not interfere with the study medication, they may be allowed at the discretion of the investigator. If the administration of any concomitant treatment is necessary it should be reported in the case record form (preferably: generic name), dosage, duration and indication for use in the patient’s medical records.

# 17. STATISTICAL DESIGN, SAMPLE SIZE ANDANALYSIS, DATA BASE

As described above, there are 3 Ayurveda plant formulations and each will be tested separately for clinical efficacy and safety as an adjunct/add-on therapy to the SOC in patients suffering from mild to moderate COVID-19 in a non-randomized, open label, parallel efficacy, active control study; active control being the arm with only SOC. The study design is exploratory in nature. This protocol will be used by each of the selected Ayurveda formulations in standalone drug trial evaluation study and in different sites.

**17.1 Sample Size:**

A convenience sample size of 70 patients in each of the arm is selected. The total sample size will be 140 patients in each of the 3 studies. The sample size is not based on any power calculations but by consensus within the experts of the Working Group constituted for the purpose of this protocol. It is assumed that the withdrawal rate may be in the range of 15-20%.

**17.2 Statistical Analysis:**

Whenever suitable, both completer and an intent-to-treat analysis with ‘last observation carried forward’ will be performed; for intent-to-treat analysis the patient should have completed at least 4 weeks of intervention and completed the follow up visit at 4 weeks post enrollment.

All statistical processing will be performed using SPSS & BMDP software unless otherwise stated.

The data will be individually analyzed for central tendencies (mean, median), range, standard error, standard deviation and 95% confidence intervals for each intervention arm in each of the groups in the study. Data will be tabulated and graphically shown using standard format and MS Excel and other software programs. Though ANOVA will be used for most of the measures, standard parametric (Student t-test) and non-parametric statistical tests (Mann Whitney statistic, Kruskal Wallis test) will be used depending upon the normality of the data. Fisher’s exact test or Chi Square will be used to test the proportion of patients classified as efficacy failures and those with AE (calculate exact binomial 95% Confidence Interval).

The primary efficacy measures of ‘mean time to clinical recovery’ and ‘proportion of patients with clinical recovery’ in the two arms will be compared using appropriate statistical tests; ANOVA for ‘mean time’ and two proportion z-test for proportion of patients.

Secondary efficacy measures in the two arms will also be compared and Bonferroni correction will be applied for multiple comparisons.

Risk ascertainment will be done for selected variables. Regression analysis (multivariate and step down) will be used to identify predictors for important outcomes. Survival analysis will be carried out to compare the two interventions (HCQ and Ashwagandha) for primary efficacy at different study time points.

Within arm efficacy will be evaluated by a one sample Student t-test.

Significance for each statistical test result will be considered at two-sided p< 0.05.

**17.3 Database:** Data will be collected from all investigation sites using both electronic transfer and paper records. A central facility will be used to enter data into a central data base by specialized personnel and under co-ordination and supervision of the sponsor. Once the data is locked, secure and specific number of copies will be made as directed by the sponsor. An authorized copy will be sent by the sponsor to the pre-designated Biostatistician for the statistical analysis and preparation of the statistical result report.

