**SECONDARY**

1. To determine the therapeutic effect of a combination of SOC plus a selected standardized Ayurvedic drug on surrogate markers of COVID-19 disease severity and complications, and recovery pertaining to broad based domain of acute phase reactants, pro-inflammatory cytokines, imaging assessment, anti-oxidant activity, organ dysfunction and damage
2. To determine the early and late post-recovery health benefits of a combination of selected standardized Ayurvedic drug plus SOC using qualitative measure of health status (WHO Quality of life assessment questionnaire) and health related behaviour, habits and fitness questionnaire
3. To describe the clinical profile of COVID-19 with special reference to early symptoms, severity of disease, complications, course of disease, diagnostic investigations, biochemical and imaging abnormalities, patterns of recovery
4. To determine the predictors of early and late recovery from COVID-19 using a therapeutic combination of SOC plus a selected standardized Ayurvedic drug

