# 9.WITHDRAWAL AND PREMATURE TERMINATION

The patient can withdraw from the study at any point of time without assigning any reason.

The study investigator can also withdraw the patient for reasons arising out of the study drug intervention such as- intervention treatment failure, progression to severe disease, requirement of critical support care (ICU), requirement of persistent oxygen support, need for ventilation, drug related toxicity, protocol violations etc. All patients withdrawing from the study will be requested to complete the formalities (including laboratory evaluation) of study completion case record form and outcome/ hospital discharge. However, they will be encouraged to continue the clinical and other assessments enumerated for post treatment study schedule in Table 1.

There are several other reasons for patient to withdraw from the study such as:

1. Patients who worsen or need ICU admission or ventilator support due to any reason
2. Non-compliance of the treatment regimen
3. Participants not willing to continue the study
4. Drug related toxicity
5. Any serious adverse event that makes the participant unable to do the activities of daily living / any SAE
6. Any other serious medical condition which the participant may acquire during the course of the trial which makes it difficult for the participant to continue in the trial
7. Any other condition which the investigator feels might cause harm to the participant

All adverse events (AE), and in particular serious adverse event (SAE) will be dealt with as described in the section on AE (see below).

The study investigator s will be required to keep an informal contact with such a study patient uptp the study completion at 12 weeks and record post study withdrawal clinical developments. The probable outcomes of such a study patient will be stated in the case record form and include asymptomatic status, days of hospitalization, symptomatic disease and its severity, time to discharge, time to recovery, death, post recovery status as stated in the patient completion case record form and outcome report

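### Last observation carried forward puts early-recovery values into the week-12 secondary results: it dilutes late effects, and biases the arm comparison if loss is unequal

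*Combined protocol and SAP*

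**What the plan says.** Section 17.2 plans, wherever suitable, "both completer and an intent-to-treat analysis with ‘last observation carried forward’ will be performed". It names no other missing-data method. The same sentence admits a patient to the intent-to-treat analysis only with "at least 4 weeks of intervention and completed the follow up visit at 4 weeks post enrollment".

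Secondary objective 2 in Section 4 is "To determine the early and late post-recovery health benefits of a combination of selected standardized Ayurvedic drug plus SOC", measured by the WHO quality-of-life and health-behaviour questionnaires. Section 8 gives regaining health as a purpose of the follow-up after recovery.

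On loss, Section 17.1 says "It is assumed that the withdrawal rate may be in the range of 15-20" per cent, with no split by arm or by time. Section 9 lists drug toxicity and non-compliance among the reasons for withdrawal, and says of withdrawn patients that "they will be encouraged to continue the clinical and other assessments enumerated for post treatment study schedule in Table 1". Section 18.2 and the section on clinical evaluation ask for a final examination at withdrawal as far as possible, with laboratory tests if possible.

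**The concern.** LOCF gives the right week-12 mean only if outcomes stop changing after the last visit attended, and this plan expects them to change. For imputed patients, the late result becomes status at the last assessment, so the early and late questions in objective 2 partly merge.

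The arms may also lose patients at different rates. Only the experimental arm takes a study drug, for 12 weeks and open label, so toxicity and tablet non-compliance arise mainly there. If outcomes are still improving, the arm with more imputed patients looks worse at week 12 than it is. Single imputation also treats the filled values as if they had been observed.

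**Working it through.** **1. Which value is carried (Appendix A, Table 1 and footnotes).**

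| Outcome | Scheduled assessments before week 12 that can be carried |
|---|---|
| WHOQOL-BREF, HR-BHF | weeks 4 and 8 |
| ESR, CRP | weeks 4 and 8 |
| Ferritin, LDH, D-dimer | week 4 (no week-8 mark) |
| Cytokine panel | discharge in the table; footnote j adds week 8 |
| SOD, GSH | discharge (no week-4 or week-8 mark) |

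A withdrawal examination, where done, would be the last value instead. Note ii to the table lets a discharge within two weeks of week 4 stand in for week 4, so a week-4 value may date from about day 14. Section 8 expects most discharges after 5 to 15 days.

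**2. Inputs.** From the documents: 70 per arm ("A convenience sample size of 70 patients in each of the arm is selected"), withdrawal of 15-20% (21 to 28 of 140), two-sided 0.05. Assumed, because the documents give nothing: the split by arm, the timing, and a later gain g of 0.5 to 1.0 SD from the carried visit to week 12.

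The plan has no power figure to reproduce: "The sample size is not based on any power calculations but by consensus within the experts". As a yardstick, the difference detectable with 80% power is (1.960 + 0.842) × √(2/70) = 0.47 SD.

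**3. Formula.** Let dD and dC be the shares imputed in the drug and SOC arms, and let E (early) and L (late) be the true effects at the carried visit and at week 12. If loss is unrelated to outcome:

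LOCF difference = (1 - dD)(g + L) + dD × E - (1 - dC) × g = (1 - dD) × L + dD × E - (dD - dC) × g

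**4. Equal loss, late-only effect (E = 0, L = 0.50 SD).**
- 15% imputed: 0.85 × 0.50 = 0.43 SD
- 20% imputed: 0.80 × 0.50 = 0.40 SD

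With equal loss and a constant effect (E = L), the formula returns L, so there is no bias.

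**5. Unequal loss: bias = -(dD - dC) × g.**
- 2:1 split of 15% (20% v 10%), g = 0.5: -0.10 × 0.5 = -0.05 SD
- 2:1 split of 20% (26.7% v 13.3%), g = 1.0: -0.133 × 1.0 = -0.13 SD
- 20% v 15%, g = 0.5: -0.05 × 0.5 = -0.025 SD

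The two 2:1 cases are upper values, with every withdrawal after week 4 and imputed from week 4. They are 11% and 28% of the 0.47 SD yardstick.

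**6. Timing.**
- Half of withdrawals before week 4: those patients leave the analysis set, and the share imputed is (d/2)/(1 - d/2). The two 2:1 cases become 11.1% v 5.3% and 15.4% v 7.1%, with bias -0.03 and -0.08 SD.
- Half of the remaining losses also after week 8, with a linear gain: multiply by 0.75, giving -0.02 and -0.06 SD.

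**7. Simulation check.** 6,000 runs, 70 per arm, correlation 0.6 between visits, all loss after week 4 with half of it after week 8, loss unrelated to outcome, no true effect. Rejection is for one unadjusted t-test.

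| Loss, drug v SOC | Gain (SD) | LOCF difference (SD) | Rejection |
|---|---|---|---|
| 17.5% v 17.5% | 0.5 | 0.00 | 4.9% |
| 20% v 15% | 0.5 | -0.02 | 5.1% |
| 25% v 10% | 0.5 | -0.06 | 6.0% |
| 25% v 10% | 1.0 | -0.11 | 10.1% |

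Unimputed week-12 data in these four scenarios gave differences near zero and 4.9-5.3% rejection. With a true effect growing from 0.10 (week 4) through 0.20 to 0.30 SD (week 12) and a 0.5 SD gain, LOCF returned 0.27 SD under equal loss and 0.21 SD at 25% v 10%.

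**The case against.** The strongest reply is that the plan already holds a safeguard. A completer analysis is planned beside LOCF, and where loss is unrelated to outcome it is unbiased, as the simulation shows. That stands. But the completer analysis drops the same patients, is unbiased only under that condition, and does not replace LOCF as the intent-to-treat rule. Outcome-dependent loss, where a mixed model has its advantage, was not simulated. The qualifier about suitability does not help, because no criterion is given.

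Section 9 and the withdrawal examination also soften the problem. Stopping tablets is not missing data: a withdrawn patient seen at week 12 needs no imputation. But continued attendance is only encouraged, and a withdrawal value is still carried to week 12 if the patient is not seen again.

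A reader might infer three stronger points that the documents do not support:
- **That LOCF always carries a week-4 or week-8 value.** Discharge and withdrawal values can be carried too, and some markers have no week-4 or week-8 sample.
- **That the false-positive rate rises well above 5%.** Rates above 10% need marked imbalance, a gain near 1.0 SD and all loss after week 4. The documents give neither split nor gain. Section 2, Table 2 puts ICU admission, ventilation and ARDS at medians of 8 to 14.5 days, so withdrawals for severe disease would mostly precede week 4. The rates are also for single tests. Section 17.2 says "Significance for each statistical test result will be considered at two-sided p< 0.05", but it also applies Bonferroni to secondary measures. That lowers the rejection rate but does not remove the bias.
- **That the primary result is affected.** Section 11.1 frames time to recovery to 28 days, before the visits that LOCF fills.

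**Conclusion.** The concern holds for later secondary outcomes and should be fixed. Following Section 17.2 mixes earlier values into the late result that objective 2 asks for.

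The dilution of a late-emerging effect needs no imbalance: 0.50 SD becomes 0.40 to 0.43 SD if 15-20% of analysed patients are imputed from a visit before the effect appears, and less is lost if fewer are imputed. The bias in the arm comparison needs both unequal loss and an outcome still changing. It is at most -0.05 to -0.13 SD in the 2:1 scenarios, roughly half that with earlier or later withdrawals, and about -0.02 SD at 20% v 15% with a 0.5 SD gain.

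The direction is also conditional. With an improving outcome, the arm that loses more patients is disadvantaged; if that were SOC, LOCF would favour the drug. Arm split, timing and gain are all assumptions, so these figures show what could happen and are not predictions. The trial's exploratory label lowers the stakes but does not make the rule fit the question.

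**What to change.** In Section 17.2, replace the LOCF phrase with wording to this effect:

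*Continuous outcomes will be analysed with a mixed model for repeated measures (arm, visit, arm-by-visit interaction, baseline value), with skewed markers log-transformed. The model will include all randomised patients with any post-baseline value and all observed values, including those collected after withdrawal under Section 9. Each outcome will use its own scheduled visits; markers measured only at discharge and week 12 will use those visits or a baseline-adjusted week-12 comparison. The week-12 contrast is the late effect; the week-4 contrast is the early effect where week 4 is measured. LOCF and completer analyses are sensitivity analyses.*

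Amend the entry clause in the same sentence, which requires four weeks of intervention and a week-4 visit. Otherwise it conflicts with using all observed values. Settle in Appendix A whether cytokines are sampled at week 8, since the table and footnote j differ.

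The cost is plan wording and a little more analysis work, with no new visits, data or patients. SPSS, already named in the plan, can fit the model. Intervals may be slightly wider than under LOCF, and the model assumes data are missing at random.

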**n. Statistical statement:**

The design of the drug trial is exploratory in nature. Though a randomized selection of patients will be done to either of the two arms, the sample size is that of convenience (expert opinion) and the same is not statistically powered however, sample size (70 patients in each arm) sufficient to draw meaningful conclusions. The statistical significance p<0.05(two sided) is predefined for analysis. Statistical analysis will be performed using standard tests to compare the two interventional arms for primary and secondary efficacy measures. Safety events will be also analyzed. Both intent-to-treat and per protocol completer analysis will be performed. Regression analysis will be done to identify predictors of response.

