The total study period is 12 weeks; Primary Efficacy is ‘Clinical Recovery’ as described in the protocol; Study participant developing severe COVID 19 or severe complication and requiring special critical support/ ICU/ ventilator support will be withdrawn from the study but followed up to record outcome; Both Ayurvedic and Allopathic Physicians will jointly examine and monitor study participants in addition to the hospital treating physician.

Patients will be selected from the outpatient or inpatient facility in COVID-19 medical centres/hospitals. The study will be explained to the volunteer patients and those willing to sign the informed consent will be screened for eligibility as per the inclusion and exclusion criteria in the protocol. Patient suffering from severe COVID-19 will be excluded (see exclusion criteria below).

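### The set called intent-to-treat is a 4-week completer set, and no analysis of all randomised patients is defined, so patients who fail before week 4 leave the comparison of both primary outcomes.

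*Combined protocol and SAP*

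**What the plan says.** Section 17.2 plans, where suitable, "both completer and an intent-to-treat analysis with" last observation carried forward (LOCF). It then restricts the second of these: "for intent-to-treat analysis the patient should have completed at least 4 weeks of intervention and completed the follow up visit" at week 4. The Synopsis (item n) says only that "Both intent-to-treat and per protocol completer analysis will be performed", without defining either set. No section names one set as primary, and none defines an analysis of all randomised patients.

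The withdrawal rules decide who can meet that condition:

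- **Section 5 (Fig 1 text):** patients with severe disease or a severe complication and "requiring special critical support/ ICU/ ventilator support will be withdrawn from the study but followed up to record outcome".
- **Section 10 and the stop rules of Section 14:** patients who develop severe disease are withdrawn. In Section 14, adverse findings attributed to treatment also lead to withdrawal, on the investigator's opinion.
- **Section 9:** the investigator may withdraw a patient for treatment failure, progression, need for intensive care or drug toxicity, among other reasons.

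Section 11.1 gives two primary outcomes: mean time from randomisation to clinical recovery, with a frame of up to 28 days, and the proportion recovered, with no time stated. On losses, Section 17.1 says "It is assumed that the withdrawal rate may be in the range of 15-20" per cent, without splitting this by arm, time or reason.

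**The concern.** An intent-to-treat analysis keeps the groups that randomisation formed. A set that requires four weeks of intervention and a week-4 visit is instead chosen by what happened after randomisation. Here that period coincides with the 28-day window of the time-to-recovery outcome. A patient who deteriorates on day 10 is withdrawn, cannot complete four weeks, and so is not counted among those who failed to recover.

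The completer analysis offers no check on this, because it leaves out the same patients. Depending on how losses fall between the arms, the filtered comparison could show a difference that does not exist or hide one that does. The condition is also hard to apply evenly: four weeks of intervention has no defined meaning for a patient on standard of care (SOC) alone who has recovered and gone home.

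**Working it through.** **Inputs from the documents.** 70 per arm and 140 in total (Section 17.1); withdrawal 15-20% (Section 17.1); two-proportion z-test for the proportion recovered, two-sided 0.05 (Section 17.2).

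**Assumptions.** True recovery of 80% in both arms, the split of early losses by arm, and the share of losses who had not recovered. The documents give none of these.

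**Step 1, the plan's own figure.** 2 × 70 = 140. There is no power calculation to reproduce; the size was set by consensus.

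**Step 2, how many could leave.** 140 × 0.15 = 21 and 140 × 0.20 = 28, leaving 119 or 112 (59.5 or 56 per arm). This is a ceiling, because the 15-20% carries no time frame and withdrawals after week 4 stay in the set. Events before week 4 are plausible: Table 2 of Section 2 cites median times of 8-12 days to ARDS, 10.5-12 days to ICU and 18.5 days to death. Those are figures from published hospital cohorts, not rates for this trial.

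**Step 3, worked example with no effect.** All randomised: 56/70 = 80% in each arm. Exclude only non-recovered patients, 14 in the drug arm and 10 in the control arm:

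- Drug 56/56 = 100%; control 56/60 = 93.3%; difference 0.0667.
- Pooled proportion = 112/116 = 0.9655.
- SE = √[0.9655 × 0.0345 × (1/56 + 1/60)] = 0.0339.
- z = 0.0667/0.0339 = 1.97, p = 0.049.

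Excluding 14 versus 7 gives 56/56 versus 56/63 (88.9%), z = 2.57, p = 0.010. Reversing the first split (10 versus 14) gives z = −1.97, so the bias can favour either arm. The 0.049 belongs to the z-test that the plan names. Fisher's exact test on the same table gives C(60,4)/C(116,4) + C(56,4)/C(116,4) = 0.068 + 0.051 = 0.119.

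**Step 4, simulation.** 200,000 trials per row, 70 per arm, true recovery 80% in both arms, pooled z-test. Analysing all randomised patients rejects in 5.0-5.2% of trials throughout. The filtered set gives:

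| Early loss, drug v control | Share of losses not recovered | Rejections | Apparent recovery |
|---|---|---|---|
| 17.5% v 17.5% | all | 3.2% | 97.0% v 97.0% |
| 17.5% v 17.5% | half | 5.1% | 86.4% v 86.4% |
| 20% v 15% | all | 38.5% | 100% v 94.1% |
| 20% v 15% | three quarters | 11.7% | 93.8% v 89.7% |
| 20% v 15% | half | 6.4% | 87.5% v 85.3% |
| 20% v 10% | all | 86.7% | 100% v 88.9% |
| 20% v 10% | three quarters | 27.2% | 93.8% v 86.1% |
| 20% v 10% | half | 9.7% | 87.5% v 83.3% |

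The rows marked all are extremes. With 80% recovery, a 20% loss made up only of non-recovered patients removes essentially every failure in that arm.

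**The case against.** The best defence has four parts. The trial is declared exploratory and unpowered. No set is called primary, and the Synopsis promises intent-to-treat without the 4-week filter. Progression, intensive care, ventilation and death are listed separately as secondary outcomes (Section 11.2), and Section 17.2 also plans a test on efficacy failures. Finally, equal losses in the two arms do not raise the false-positive rate.

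Some of this stands. The severe outcomes do have their own endpoints. A reader might infer that harm acting through progression would be invisible in this trial; the documents do not support that. The analysis set for those endpoints is not stated, so they may be affected, but what is shown concerns the primary comparison. It is also right that inflation needs unequal losses, for which the documents give no figure.

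The rest does not rescue the rule. The Synopsis defines no set, so Section 17.2 is the only operative definition. Exploratory status does not remove the planned testing: "Significance for each statistical test result will be considered at two-sided p< 0.05". The survival analysis in Section 17.2 states no population and names two treatments that are not under test here, so it is no safeguard.

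Three further inferences should be resisted:

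- **LOCF carries pre-deterioration values into the primary result.** It does not. Patients lost before week 4 are never in the set, and those in it have attended week 4.
- **Every treatment failure must be withdrawn.** Only severe disease or critical support carries mandatory wording; Section 9 is discretionary on treatment failure.
- **The rule demonstrably acts harder on the drug arm.** The plan refers to both arms as interventional, so four weeks of intervention could mean four weeks on the assigned arm. What can be said is that the term is undefined for SOC alone.

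**Conclusion.** The definition is wrong as written, not merely short of detail. Following Section 17.2 removes patients who fail before week 4 from the comparison of both primary outcomes, and no other planned set brings them back. The same text governs all three drug trials.

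The number removed is at most 21-28 of 140 per trial, on the assumption that every expected withdrawal happens before week 4; the true number cannot be derived from the documents. With equal losses of 17.5%, recovery is overstated (86-97% against an assumed 80%) but the false-positive rate is not raised. With losses of 20% against 15%, the false-positive rate is 6.4% if half of those lost had not recovered and 38.5% if all had not. A reader might take these figures to mean that a false-positive result is likely. They show only what the rule permits under assumed loss patterns.

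**What to change.** 1. In Section 17.2, define intent-to-treat as all randomised patients analysed in the arm assigned, with no minimum exposure and no required visit. Name it as the set for both primary outcomes, and put the same definition in the Synopsis.
2. State that outcome follow-up and analysis continue whether or not a patient is still on study drug. This concerns analysis only and leaves the rules on stopping treatment as they are.
3. Make collection of Day-28 recovery and vital status firm for withdrawn patients. Section 9 now describes only informal contact, and Section 10 says investigators are encouraged to follow up. Clinical recovery needs 48 hours of physician observation and a blinded assessor (Section 11.1), which informal contact may not supply.
4. Count patients who die, or who progress and have no documented recovery by Day 28, as not recovered. Use recorded recoveries where they exist, including those after progression. Give the proportion outcome the same Day-28 time point.
5. Keep the present set, relabelled as a 4-week completer sensitivity analysis, and say what four weeks of intervention means in the SOC arm.

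The cost is mostly wording, plus some extra follow-up effort to secure Day-28 status. The estimate may become less favourable to the study drug.
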